**Influence of cardiopulmonary bypass pump on selenium status of cardiac surgical patients, undergoing coronary artery bypass surgery.**

*Inclusion criteria:*

100 patients, undergoing open heart surgery should be included in the trial. Here, 50 patients will be operated conventional, with the use of CPB and cardioplegia. Further 50 patients will be operated on the beating heart, without the use of CPB (OPCAB= „off pump coronary artery bypass“). The surgeon ([name]) will perform the surgery in all patients.

Included will be all patients suffering from a coronary 3-vessels heart disease. They will undergo surgery in general anaesthesia with median sternotomia in the case of elective or urgent indication for treatment. Patients should be free of further serious cardiac diagnoses (valve-disease, aneurysms etc.). Excluded are patients with ischemic cardiomyopathy. The aimed revascularization should be completely performed and conducted by one surgeon. 50 patients are undergoing conventional surgery, with the use of cardiopulmonary bypass (CPB), with moderate hypothermia and cardioplegic cardiac arrest. The other 50 patients will be treated without the use of CPB (OPCAB).

Only adults, after written informed consent for the study participation will be included.

*Exclusion criteria:*

Excluded will be patients with emergency surgery (NSTEMI or STEMI), patients with ischemic cardiomyopathy or additional cardiac diagnoses (valve-diseases or aneurysms), patients incapable of giving consent, pregnant patients and women with childbearing potential, in which pregnancy cannot be excluded.

Patients will be enrolled in the clinical trial, after patient information, at least, the evening before the operation.

*Methodology of study:*

After induction of anaesthesia, within one hour after admission the patient to the intensive care unit and every further morning on the intensive care unit or intermediate care unit (IMC), 10 ml blood will be drawn from the central venous line, placed independently of the study for the operation. A separately puncture for this purpose it is not necessary.

Selenium values will be measured from this blood in the whole blood sample by electrothermal atomic absorption spectroscopy.

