Beside this, the following parameters will be measured daily in the routinely diagnostic and later correlated with the selenium concentration at the respective time points. The measurement of glutathione peroxidase (GPX) und thioredoxin (TRX) reductase will be conducted in the laboratory of the company Biosyn. The „macrophage migration inhibitory factor (MIF)“ will be determinated from the remaining blood.

*Determinated parameters:*

- Procalcitonin
- CRP
- IL-6, IL-10
- Leukozyten
- Glutathione peroxidase (GPX)
- Asymmetric dimethylarginin (ADMA)
- Thioredoxin reductase (TRX)
- Platelets
- Bilirubin
- Creatinine
- Lactat
- Albumine
- AT-III
- CK, CKMB and troponin
- Duration of mechanical ventilation
- Duration of hospitalisation
- SOFA-Score
- SAPS-Score

All blood samples will be kept until study end and their analysis (max. 24 months) and will be disposed thereafter.

Values of selenium, markers of oxidative stress (GPX, ADMA) and inflammation (IL-6, IL-10) from the 1.POD on will be used for possible long-term analyses of selenium course.

All data will be recorded on a documentation form.

*Study duration:*

The study will be terminated, as 100 patients are included or after a maximum of 24 months.

*Risks:*

Patients are not exposed to additional risk by blood sampling before surgery, after admission to intensive care unit, and every further day on the intensive care unit. All blood samples will be drawn from catheter, placed independently of study participation, for cardiovascular monitoring. Therefore blood sampling for this study is not associated with pain.

Summarized, according to current scientific evidence there is not expected an impairment or additional stress for the participating patients.

*Benefits:*

There is no benefit for the individual participant of the study expected.

Significant low selenium values (lower than the reference value of selenium in whole blood of 100-140µg/L) will be detected.

*Statistic:*

All data will be recorded pseudonymized and analyzed anonymized.

Recorded patient data will be anonymized, by numbering in order of study inclusion. Thereafter the mean and standard deviation of the recorded data will be calculated and this data will be further statistically evaluated.

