Hereby the correlation of measured selenium blood values and laboratory chemical parameters of inflammation and the clinical patient outcome will be evaluated. Differences between the groups (OPCAB vs. conventional CPB-surgery) concerning the laboratory chemical and clinical course will be statistically analyzed by tests comparing independent groups. Correlations between the different variables will be analyzed by the methods of Pearson and Spearman-rho. The predictive value of selenium blood levels concerning certain outcome parameters will be determined by the receiver-operating characteristic curves (ROC).

*Quality assurance:*

This observational study will be conducted under the Good Clinical Practice guidelines.

*Adresses and responsibilities:*

Scientific direction:

PD [name]

Senior consultant

Department of Anaesthesiology

University Hospital Aachen

[name]

[name]

Direct line - [contact]

[contact] (secretariat)

[contact]

E-Mail: [contact]

Involved physicians:

[name], Senior consultant, Department of Thoracic, Cardiac and Vascular Surgery

[name] (direct line: [name]), resident physician, Department of Anaesthesiology

Laboratory:

biosyn Arzneimittel GmbH

[name]

[name]

Telefon: [name]

Telefax: [name]

[contact]

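### Ventilation time and hospital stay serve as clinical outcomes, but death is not among the listed parameters, so an early death would read as a fast recovery

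*Protocol*

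**What the plan says.** The list under *Determinated parameters* in the protocol consists of laboratory values and four clinical items: "Duration of mechanical ventilation", "Duration of hospitalisation", and the SOFA and SAPS scores. Death, survival and discharge status are not on it. The words death and mortality occur nowhere in the protocol.

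The *Statistic* section then uses the recorded values in this order:

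- Summary: "Thereafter the mean and standard deviation of the recorded data will be calculated and this data will be further statistically evaluated".
- Correlation (Pearson and Spearman): the relation of selenium to "laboratory chemical parameters of inflammation and the clinical patient outcome will be evaluated".
- Group comparison of the laboratory and clinical course, OPCAB against CPB: differences "will be statistically analyzed by tests comparing independent groups".
- ROC curves for selenium as a predictor of outcome parameters that are not named.

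No step says what happens to the two durations when a patient dies. The protocol also does not say from which day the hospital stay is counted.

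**The concern.** On both durations a smaller value reads as a better result. That holds only for patients who leave the ventilator or the hospital alive. A patient who dies on day 1 or 2 after surgery has one of the shortest stays in the study, and possibly a short ventilation time. Without a death field, that patient cannot be told apart from one who recovered quickly.

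Two analyses are exposed. If low selenium goes with a poor course, early deaths put some of the worst courses at the favourable end of the outcome scale and pull the correlation towards zero. In the group comparison, the technique with more early deaths gains an apparent advantage in length of stay.

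SOFA and SAPS do not remove the problem. Neither records death, and daily scoring stops when the patient dies.

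Handling rules for deaths can be left to an analysis plan. Such a plan can only apply them, however, if death is collected, and the list of what is collected is a protocol matter.

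**Working it through.** The protocol gives no mortality rate, effect size, standard deviation or power, and it does not derive its 100 patients. There is therefore no stated figure to reproduce, and everything below except the sample size is an assumption.

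**1. Is a death likely to occur?** The *Inclusion criteria* state: "100 patients, undergoing open heart surgery should be included in the trial", 50 per technique. With assumed in-hospital mortality p, the chance of at least one death is 1 − (1 − p)^100.

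| Assumed p | Expected deaths | P(at least one) |
|---|---|---|
| 1% | 1 | 1 − 0.99^100 = 63% |
| 2% | 2 | 1 − 0.98^100 = 87% |
| 3% | 3 | 1 − 0.97^100 = 95% |
| 5% | 5 | 1 − 0.95^100 = 99% |

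These are deaths at any time in hospital. Only the early ones create the problem.

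**2. Effect on the selenium–stay correlation.** Inputs, all assumed:

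- n = 100, with selenium and latent severity bivariate normal and correlated at -0.30.
- Stay = 10 × exp(0.4 × severity) days, that is, lognormal with median 10 days and log-SD 0.4.
- Patients who die get a stay of 1 to 3 days.

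For a Pearson correlation of -0.30, the population Spearman value is (6/π) × arcsin(-0.30/2) = -0.288. This is the reference, and simulated means without deaths lie at about -0.28 to -0.29. The results depend on who dies. In scenario A the patients with the highest severity die. In scenario B those most extreme jointly on low selenium and high severity die.

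| Early deaths | A: deaths as short stays | B: deaths as short stays | Deaths ranked worst (A or B) |
|---|---|---|---|
| 1 | -0.26 | -0.23 | about -0.28 to -0.29 |
| 2 | -0.24 | about -0.18 to -0.19 | about -0.28 to -0.29 |
| 3 | -0.22 | -0.14 | about -0.28 to -0.30 |

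Ranges within a cell reflect separate simulation runs with 2,000 to 4,000 replicates each. If the probability of death only rises with severity (weight exp(severity)), the values are milder still: -0.27, -0.26 and -0.25. If deaths are unrelated to severity, shortest-stay and worst-rank scoring do not differ.

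**3. Effect on the group comparison.** The assumed stay distribution has mean 10 × exp(0.4²/2) = 10.8 days. If d patients in a group of 50 die on day 2, the group mean shifts by d × (2 − 10.8)/50:

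- d = 1: -0.18 days
- d = 2: -0.35 days
- d = 3: -0.53 days

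The shift favours the group with more early deaths.

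**4. When the effect vanishes.** With d = 0 there is nothing to distort. A patient who dies after a long intensive care stay already has a long duration and sits near the unfavourable end.

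**The case against.** The strongest reply is that this belongs to the analysis plan. How a death enters a duration, and from which day a stay is counted, are derivation rules that protocols commonly leave to a later document. That stands for the rules. It does not stand for the missing status, because no later rule can be applied to a variable that the protocol does not list for collection.

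Several stronger readings are tempting, and the documents do not support them:

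- **That death is certainly not recorded anywhere.** The protocol refers to a documentation form that is not shown, and it speaks of clinical outcome in general terms. What can be said is that death is absent from the parameter list.
- **That the durations feed the ROC curves.** The protocol says only: "The predictive value of selenium blood levels concerning certain outcome parameters will be determined by the receiver-operating characteristic curves (ROC"). The outcomes are not named. Even if a stay above 14 days were used, the AUC in the simulation of scenario A moves only from about 0.65 to 0.64–0.63 for 1 to 3 deaths.
- **That the correlation could change sign.** This is not shown. In scenario B with 4 deaths it is still -0.09.
- **That scenario B is the expected case.** It is the extreme one. When simply the sickest die, about half of that attenuation remains.
- **That the stay by definition includes pre-operative days.** This is one reading of an undefined term. The protocol admits both elective and urgent cases, so the start day could matter, but it gives nothing from which to size the effect.

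It is also fair to say that the population is selected: emergency surgery, ischaemic cardiomyopathy and additional cardiac diagnoses are excluded, so deaths may be few. The title question, the influence of CPB on selenium, does not depend on these durations.

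**Conclusion.** The point holds in limited form. Followed as written, the protocol records an early death as a short, favourable duration, and it lists no variable by which the error could be detected or corrected.

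For 1 to 3 early deaths, the rank correlation loses roughly 0.03 to 0.07 in absolute value if the sickest patients die (0.29 − 0.26 and 0.29 − 0.22). In the extreme scenario the loss is 0.06 to 0.15 (0.29 − 0.23 and 0.29 − 0.14). The mean stay of a group moves by about 0.2 to 0.5 days. All of this rests on assumed mortality, an assumed correlation of -0.30, an assumed stay distribution and an assumption about who dies.

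The distortion is confined to the outcome correlations and to the comparison of clinical course. The comparison of selenium and biomarkers between techniques stands. The change is worth making because it is cheap and because the status may be hard to recover after the planned anonymisation.

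**What to change.** 1. Add in-hospital death, with status and date, to the parameter list and to the documentation form.
2. Report the number of deaths in each surgical group.
3. In rank-based analyses of the two durations (Spearman, rank tests), give in-hospital deaths the worst rank. Add a survivors-only sensitivity analysis.
4. Report Pearson correlations and means of the two durations in survivors, next to the death counts, because worst-rank scoring does not carry over to them.
5. Define the hospital stay as counted from the day of surgery.

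The cost is one extra entry on the form (status with date), with no additional blood sampling and no follow-up after discharge. The limitation is that survivors-only figures compare selected patients and must be read with the death counts.

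Replacing the durations with ventilator-free days or days alive and out of hospital over 28 or 30 days is less suitable here. If most patients are extubated within a day (an assumption), ventilator-free days would crowd at the ceiling. Days alive and out of hospital would need follow-up after discharge, which the protocol does not schedule.

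### No main variable, time point or contrast is fixed for the CPB versus OPCAB comparison across 23 repeatedly measured variables, so false-positive group differences are likely and the selenium time point stays open.

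*Protocol*

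**What the plan says.** The title of the protocol is "Influence of cardiopulmonary bypass pump on selenium status of cardiac surgical patients, undergoing coronary artery bypass surgery". The Inclusion criteria section sets the size: "100 patients, undergoing open heart surgery should be included in the trial", of whom "50 patients will be operated conventional, with the use of CPB and cardioplegia" and the other 50 have OPCAB. No random allocation is described, and the Quality assurance section calls the study observational.

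Under Methodology of study, blood is drawn after induction of anaesthesia and then "within one hour after admission the patient to the intensive care unit and every further morning on the intensive care unit" or intermediate care unit. The number of samples per patient is therefore open. Selenium is measured in this blood. For the rest, "the following parameters will be measured daily in the routinely diagnostic and later correlated with the selenium concentration at the respective time points". The list that follows holds 21 parameters; MIF is added outside it.

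The Statistic section plans three kinds of analysis:

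- Group comparisons of the laboratory and clinical course, by "tests comparing independent groups".
- Correlations, by both Pearson and Spearman: "the correlation of measured selenium blood values and laboratory chemical parameters of inflammation and the clinical patient outcome will be evaluated".
- ROC curves for selenium against outcomes that are not named.

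It states no primary variable, main time point, significance level or order of importance.

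**The concern.** The title's question can be answered at ICU admission, on any later morning, as a change from the post-induction value, or over the whole course. The Statistic section chooses none of these. An analyst can follow it to the letter and still decide, after seeing the data, which selenium comparison to present as the result. The same freedom covers 22 other variables.

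Two things are at stake. First, some group differences will probably look significant by chance, and nothing in the protocol lets a reader tell these from the result the study was set up to obtain. Second, the groups are not described as randomised, so they may differ in selenium before surgery. The study collects the value needed to allow for this, but the plan for the group comparison does not mention it.

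**Working it through.** The protocol gives no significance level, effect size or power, so it has no figure to reproduce. **Assumptions:** two-sided 5% per test; no true difference in any variable; one test per variable and time point. The last is a reading of the plan, not its wording.

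**1. Variables** (Methodology of study and the parameter list). PCT, CRP, IL-6, IL-10, leukocytes, GPX, ADMA, TRX, platelets, bilirubin, creatinine, lactate, albumin, AT-III, CK, CK-MB and troponin make 17. Ventilation time, hospital stay, SOFA and SAPS make 4.
- Listed: 17 + 4 = 21. With selenium and MIF: 21 + 2 = 23.
- Repeated, leaving out SAPS and the two durations: 23 − 3 = 20.

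**2. Times that can show an effect of bypass.** The post-induction sample precedes bypass, so a difference there is baseline imbalance. Counting only ICU admission and the first morning after surgery gives 20 × 2 = 40 tests. Longer stays add more.

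**3. Expected false positives** = k × 0.05. This does not depend on correlation between tests.
- k = 40: 40 × 0.05 = 2.0.
- k = 23 (one test per variable): 23 × 0.05 = 1.15.

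**4. Chance of at least one.** Under independence it is 1 − 0.95^k. For correlated tests I used equicorrelated normal test statistics; the correlations are assumed.

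| Tests | Independent | Correlation 0.3 | Correlation 0.5 |
|---|---|---|---|
| 40 | 0.87 | 0.74 | 0.57 |
| 23 | 0.69 | 0.58 | 0.45 |

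**5. Two correlation methods.** In 5,000 simulated null data sets of 100 patients, declaring a correlation when either Pearson or Spearman was significant raised the error per pair from 5% to about 6.6% (normal data) or 8.8% (lognormal data).

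**6. What one main comparison can detect.** With 50 per group and 80% power, before baseline adjustment, the detectable difference is (1.960 + 0.842) × √(2/50) = 2.802 × 0.2 = 0.56 SD. The false-positive risk for that comparison is 5%. A Bonferroni correction over 23 tests would raise the detectable difference to 0.78 SD.

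**The case against.** The strongest reply is that selenium is plainly the lead variable. It is in the title, its measurement is described first, and the other parameters are introduced as additions. Values from the first post-operative day onwards are set aside for possible long-term analyses, which hints that the earlier samples are the core. The study is observational and makes no confirmatory claim, and the significance level, any multiplicity correction and the choice of correlation coefficient may sit in an SAP that is not shown.

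Much of this stands. The absence of a multiplicity procedure is not a fault of the protocol. What remains is that neither title nor text fixes a time point or contrast for selenium. That choice defines the study's question and belongs in the protocol. An observational design does not remove the room for selective reporting, and nothing in the document calls the analyses exploratory.

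A reader might go further and infer that false effects of CPB are near certain, or that several will be reported. The documents do not support this:

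- The 5% level is assumed; the protocol does not state that all tests carry equal weight at 5%.
- A test at each time point is inferred. The Statistic section speaks of the course, and only the correlations are tied to particular times.
- Adding the post-induction sample gives 60 tests and a chance of 95% under independence, but those 20 extra tests precede bypass. Even with all 60, the chance of three or more false positives is about 0.58, 0.42 and 0.31 at correlation 0, 0.3 and 0.5.
- Correlations and ROC curves relate selenium to other variables. They can mislead, but they cannot produce a false group difference. Pearson and Spearman on the same pair are also not two separate tests.

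**Conclusion.** The point holds in a limited form. The protocol turns its title into no defined comparison: no main variable, time point or contrast is fixed among 23 variables, and post-induction selenium is given no part in the group comparison. At an assumed 5% per test with no true effect, expect about 1 to 2 false-positive group differences (1.15 for 23 tests, 2.0 for 40). For 40 tests the chance of at least one is about 57% to 87%, depending on correlation. False positives are likely, not near certain. The open choice of selenium time point matters as much as the count and needs none of these assumptions. The arithmetic covers chance alone; bias from non-random groups would come on top. The change should be made, but the planned data collection is sound for it.

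**What to change.** Add to the Statistic section:

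- **Main comparison:** whole-blood selenium in the sample taken within one hour of ICU admission, CPB versus OPCAB, adjusted for the post-induction value (for example by a linear model with group and post-induction selenium), two-sided 5%.
- **Everything else:** other group comparisons, correlations and ROC analyses are exploratory and reported as estimates with 95% confidence intervals. Choose one correlation method in advance.

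This costs a few sentences and needs no extra blood sample or patient, since both selenium samples are already planned. The price is that differences in other laboratory or clinical variables can no longer be claimed as confirmatory. Adjustment for post-induction selenium deals with baseline imbalance in selenium only; other differences between the groups remain a limitation to be stated.

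### The group comparison of a serially measured course is assigned to tests for independent groups, with no per-patient summary, baseline adjustment or longitudinal method named

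*Protocol*

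**What the plan says.** Under Methodology of study, the protocol draws blood after induction of anaesthesia and then "within one hour after admission the patient to the intensive care unit and every further morning on the intensive care unit" or IMC. Each patient therefore contributes several selenium values, and the number grows with length of stay. The same section has the routine laboratory parameters measured daily and "later correlated with the selenium concentration at the respective time points".

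Under Statistic, the data are summarised by mean and standard deviation. Differences between OPCAB and CPB patients "concerning the laboratory chemical and clinical course will be statistically analyzed by tests comparing independent groups". The other methods are for association and prediction: "Correlations between the different variables will be analyzed by the methods of Pearson and Spearman-rho", and ROC curves for the predictive value of selenium. Values from the first post-operative day on are reserved for possible longer-term analyses of the selenium course, with no method given.

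The groups are fixed at 50 patients each: "50 patients will be operated conventional, with the use of CPB and cardioplegia. Further 50 patients will be operated on the beating heart". They are not described as randomised.

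**The concern.** The title asks how the bypass pump influences selenium status. That is a comparison between groups of what happens from before to after surgery. The only group analysis named is a class of tests that takes one value per patient, and the protocol does not say which value or values enter it.

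The sentence can be carried out in at least three ways, of very different quality:

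- **A separate test at each time point.** Each test is valid. A row of p-values does not show whether the courses differ, and the patient's own starting value plays no part.
- **One test on all samples pooled.** Repeated samples from one patient then count as separate patients, those with long stays weigh most, and standard errors are too small.
- **One test on a per-patient summary**, such as the change from the post-induction value. This is sound.

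The protocol does not choose among them. What is at stake is the error rate of the main comparison and how much information 100 patients can yield.

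**Working it through.** **Inputs from the protocol.** 50 patients per group (Inclusion criteria). At least two scheduled samples per patient, then one each morning on ICU or IMC (Methodology of study).

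**Inputs not in the protocol, assumed here.** Two-sided 5% level; k samples per patient, k = 2 to 4; equal correlation rho between any two samples of a patient, 0.3 to 0.7; a post-operative difference of 0.5 SD; no group difference at the post-induction sample. The sample size is stated without level, power, effect or SD, so there is no figure to reproduce. For orientation, 50 per group detects (1.96 + 0.84) × sqrt(2/50) = 0.56 SD with 80% power at one time point.

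**1. Separate tests per time point, no true difference.** Each test holds 5%. The chance of at least one significant result per variable was simulated (10,000 runs), counting the post-induction sample as a time point:

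| Time points | rho 0.5 | rho 0.7 | if independent |
|---|---|---|---|
| 3 | 12.5% | 10.5% | 1 − 0.95³ = 14.3% |
| 4 | 15.7% | 12.8% | 1 − 0.95⁴ = 18.5% |

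Counting only the post-operative tests gives 9.1% and 8.1% (two tests), and 12.6% and 10.6% (three tests).

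**2. All samples pooled, no true difference.** The variance of a group mean is understated by the factor 1 + (k − 1)rho, so the false-positive rate is 2 × [1 − Φ(1.96 / sqrt(1 + (k − 1)rho))].

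| k | rho 0.3 | rho 0.5 | rho 0.7 |
|---|---|---|---|
| 2 | 8.6% | 11.0% | 13.3% |
| 4 | 15.5% | 21.5% | 26.6% |

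For k = 4 the simulation gave 21.7% at rho 0.5 and 26.4% at rho 0.7, in agreement.

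**3. Power for a constant 0.5 SD difference.**

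- One time point, unadjusted: noncentrality 0.5 / sqrt(2/50) = 2.50, power 70% (98 df).
- Three samples in total, with the mean of the two post-operative values adjusted for the post-induction value. The residual variance in SD² units is (1 + rho)/2 − rho².
  - rho 0.5: 0.75 − 0.25 = 0.50; noncentrality 0.5 / sqrt(2 × 0.50/50) = 3.54; power 94% by formula, 93% simulated.
  - rho 0.7: 0.85 − 0.49 = 0.36; noncentrality 4.17; power 98% by both.
- An independent-groups t-test on each patient's change (post-operative mean minus post-induction value), three samples in total: type I error 4.9%, power 81% at rho 0.5 and 96% at rho 0.7 (simulated).

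**4. If the difference does not last.**

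- Suppose it is 0.5 SD at ICU admission and zero afterwards. The mean of two post-operative values then differs by 0.5/2 = 0.25 SD. The adjusted analysis has noncentrality 0.25 / sqrt(2 × 0.50/50) = 1.77 at rho 0.5, power about 42%. A single unadjusted test at ICU admission has 70%, so the ranking reverses.
- With three post-operative samples, no baseline adjustment and rho 0.5, the averaged difference is 0.5/3 = 0.167 SD and the variance (1 + 2 × 0.5)/3 = 0.667. Noncentrality is 1.02 and power 17%.
- If the difference instead halves at each of those three samples, the averaged difference is (0.5 + 0.25 + 0.125)/3 = 0.292 SD and power about 42%.

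**The case against.** Bypass and off-pump patients are different people, so a test for independent groups is the right kind of test once each patient is reduced to one value. A reader might infer that the protocol forces a choice between pooling the samples and discarding the within-patient information. It does not: a test on change or on a post-operative mean fits the wording, holds 5%, and does address the course. That part of the objection stands.

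A reader might also infer that samples will be pooled and that false positives are therefore to be expected. The documents do not support this. Pooling is stated nowhere, and for the marker correlations the wording about respective time points leads away from it. The group-comparison sentence carries no such wording, so pooling is left open there, and the figures in step 2 are conditional on it.

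The power gain is not guaranteed either. It rests on an assumed lasting difference, and step 4 shows it can reverse. The number of samples and the within-patient correlation are assumptions throughout.

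Finally, a longitudinal model and its covariance structure are commonly left to an SAP, and none is shown here. That would settle the matter if the protocol were silent. It is not silent: it names a class of tests for the course. An SAP with a mixed model would depart from that sentence, so the sentence needs amending in either case.

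**Conclusion.** The point holds as a badly fixed analysis, not as a demonstrated error in the results. The protocol collects a series per patient and assigns the group comparison of that series to tests that, by themselves, neither use the repeated values nor test group-by-time. It names no summary, baseline adjustment or model to close the gap.

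Under the likeliest literal reading, separate tests per time point, the cost is threefold: no test of the course, an unused post-induction value, and about 10% to 16% familywise error per variable over 3 to 4 time points at rho 0.5 to 0.7. If samples were pooled, false positives would be about 9% to 13% with 2 samples and 16% to 27% with 4, at rho 0.3 to 0.7. Power of about 70% against 93% to 98% applies only to a constant 0.5 SD difference with rho 0.5 to 0.7 and no baseline imbalance.

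The change is worth making because it is cheap and uses data the study already collects.

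**What to change.** In the Statistic section, replace the independent-groups sentence, for all serially measured variables, with one of these:

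- a mixed model for repeated measures with group, time point, group-by-time and the post-induction value as covariate, and a stated within-patient covariance; or
- one named per-patient summary, for example the baseline-adjusted post-operative value, compared between groups.

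Further points to write in:

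- Limit the analysis to an early window, stated in advance, in which nearly all patients are still sampled. Sampling ends at ICU/IMC discharge, so later gaps depend on the clinical course. A short window also limits the dilution shown in step 4.
- Keep simple independent-group tests for variables with one value per patient, such as ventilation time and hospital stay.
- Analyse selenium-marker correlations per time point or with a repeated-measures method.
- Enter exactly one pre-specified selenium value per patient in correlations with once-per-patient outcomes and in ROC analyses.

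The cost is a few sentences and modest analysis work, with no added patients or samples. The downsides are that a covariance structure and a time window must be chosen, and that the mixed model assumes missing later samples are ignorable given the observed data. Baseline adjustment sharpens the before-to-after comparison but does not remove other differences between groups that are not described as randomised.
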